# Abbreviations

| ACTIV | *Association clinique thérapeutique infantile du Val de Marne* [Val de Marne Infant Clinical and Therapeutic Association] |
| --- | --- |
| CRA | Clinical Research Associate |
| CHIC | *Centre Hospitalier Intercommunal de Créteil* [Intercommunal Hospital of Créteil] |
| CRC | Clinical Research Centre |
| PI | Principal Investigator |
| RIPH | *Recherche interventionnelle sur la personne humaine* [Interventional Research on Humans] |
| CST | Clinical Study Technician |
| GPIP | *Groupe de Pathologie Infectieuse Pédiatrique* [French Paediatric Infectious Disease Group] |

# Project summary

| **General characteristics** | | |
| --- | --- | --- |
| Study acronym | SEINE | |
| ID-RCB Number | **2020-A00857-32** | |
| Clinical Trials Number | NCT04685850 | |
| Sponsor | Intercommunal Hospital of Créteil | |
| Regulatory | | |
| Study type | Study with minimal risks and obligations involving human subjects (RIPH2) | |
| Number of sites | 56 hospital departments in Ile de France | |
| Methodology | A multi-centre, prospective, non-randomised study of patients who had an invasive meningococcal infection (IMI) such as meningitis or meningococcal purpura fulminans diagnosed in a hospital paediatric department in Ile de France between 2010 and 2019. | |
| **Research design** | | |
| Population involved | Children aged 1 to 15 years who had meningitis or meningococcal purpura fulminans between 2010 and 2019 | |
| Rationale and background | The occurrence of an IMI, mainly meningitis, is of concern not only to healthcare professionals but also to the general population, in whom this condition justifiably remains a major worry. Thanks to the monitoring networks supported by the French National Public Health Agency [Santé Publique France] (Meningococci CRN, Epibac network), we have reliable data on incidence and mortality in France. The same is not true for the sequelae. Due to its methodology, the French Observatory of Bacterial Meningitis in Children [Observatoire des Méningites Bactériennes de l’Enfant] established in 2001 by the French Paediatric Infectious Disease Group (GPIP) allows for a short-term approach to sequelae. In contrast, the assessment of more long-term sequelae, on the clinical level and on the intellectual, sensory and learning development level, requires patients to be followed-up for a minimum of one year after the onset of the disease.  The French Observatory of Bacterial Meningitis in Children identified 7,624 cases of meningitis and purpura fulminans from all bacteria between 2001 and 2019 from 233 participating paediatric departments. In Ile de France, 56 general paediatric, neonatal medicine and paediatric intensive care departments made up 22% of this cohort. If the period from 2010 to 2019 is considered, 169 cases of meningitis and meningococcal purpura fulminans were identified (15 to 20 cases per year); nine patients died, 36 experienced short-term sequelae, 21 had neurological complications, eight had circulatory complications and seven presented with other involvement. A recent survey carried out with the relevant departments in Ile de France showed that the patients were, on average, seen again one year after the episode, and that some of them had sequelae (intellectual or physical) which were not initially identified at the time the patient was discharged from hospital.  Thus, by selecting only the Ile de France region (representative of the rest of France), the observational data could be used to implement a prospective study which would allow for a more specific approach to the long-term sequelae of childhood meningitis and meningococcal purpura fulminans. This would specifically include clinical, psychological and psychomotor assessments and a speech assessment. In addition, a survey addressed to the parents should help to assess their experience with the disease, to identify post-traumatic stress, and to review the care pathway which had (or had not) been implemented since their child was discharged from hospital. The perception of the relatives regarding the consequences of these serious conditions, such as amputations and their medical and logistical care, might thus also be described. | |
| Expected results | Few studies have reported on the long-term sequelae of childhood IMIs, such as meningitis and purpura fulminans, at least one year after, and up to a maximum of ten years after, their discharge from hospital. In terms of public health, this study should highlight the importance of a “flagged“ care pathway in these serious conditions which sometimes have delayed consequences. | |
| Calculation of the number of patients | Between 2010 and 2019, 169 cases of meningitis and meningococcal purpura fulminans were declared in the French National Observatory of Bacterial Meningitis in Children. After having excluded deceased patients (n = 9) and patients who have been lost to follow-up (approximately 20%, n = 30), and with an envisaged acceptance rate of 80%, 100 patients should be enrolled and follow the care pathway established as part of the study. | |
| Primary objective | To assess the long-term (between one and ten years) physical, neurological or sensory sequelae of meningitis or meningococcal purpura fulminans | |
| Primary endpoint | - Number of children with at least one neurological, orthopaedic or sensory sequela | |
| Secondary objectives | - To establish a care pathway extending beyond one year of follow-up - Assessment of parental post-traumatic stress - To assess the social impact of the disease: education of the children; activity of the parents | |
| Secondary endpoints | - Number of children who underwent a “flagged“ care pathway with the establishment of a score based on the consultations performed - Number of children with severe neurological sequelae: hemiplegia etc. - Number of children with orthopaedic complications (amputations etc.) - Number of children with sensory disorders - Number of children with skin sequelae - Number of children with learning disabilities (with no identified neurological sequelae) - Number of children with cognitive or psychological impairments identified on the WPPSI, WISC V or VINELAND - Care pathway followed by the children: number and type of follow-up consultations (Specialised paediatric consultations or not; ENT and speech therapy assessment/follow-up; neurodevelopmental assessment) - Parental post-traumatic stress assessment via the IES-R questionnaire | |
| Inclusion criteria | - Infants and children 1 to 15 years of age - Having had meningitis or meningococcal purpura fulminans included in the observatory between 2010 and 2019 - Those with parental authority have read and understood the information letter and their express consent was obtained - Patient affiliated with a social security scheme (Social Security or French Universal Medical Coverage) | |
| Exclusion criteria | - Refusal of either parent | |
| Performance of the study | | |
| Patient pathway | [figure not shown] | |
| Study schedule | Planned start date of the study | Q4 2020 |
|  | Planned enrolment end date | Q2 2023 |
|  | Duration of the enrolment period | 2 years |
|  | Duration of patient follow-up in the study | 1 year |
|  |  | |
| Publications/Communications | Publication in a peer-reviewed medical journal  Presentation of the study (oral or poster) at a conference | |

# Research rationale and background

Research hypothesis

The occurrence of invasive meningococcal infections (IMI), mainly meningitis, is of concern not only to healthcare professionals but also to the general population, in whom this condition justifiably remains a major worry. Thanks to the monitoring networks supported by the French National Public Health Agency (Meningococci CRN, Epibac network), we have reliable data on incidence and mortality in France. The same is not true for the sequelae. Due to its methodology, the French Observatory of Bacterial Meningitis in Children established in 2001 by the French Paediatric Infectious Disease Group (GPIP) allows for a short-term approach to sequelae. In contrast, the assessment of more long-term sequelae, on the clinical level and on the intellectual, sensory and learning development level, requires patients to be followed-up for a minimum of one year after the onset of the disease.

The French Observatory of Bacterial Meningitis in Children identified 7,624 cases of meningitis and purpura fulminans from all bacteria between 2001 and 2019 from 233 participating paediatric departments. In Ile de France, 56 general paediatric, neonatal medicine and paediatric intensive care departments made up 22% of this cohort. If the period from 2010 to 2019 is considered, 169 cases of meningitis and meningococcal purpura fulminans were identified (15 to 20 cases per year); nine patients died, 36 experienced short-term sequelae, 21 had neurological complications, eight had circulatory complications and seven presented with other involvement. A recent survey carried out with the relevant departments in Ile de France showed that the patients were seen, on average, one year after the episode, and that some of them had sequelae (intellectual or physical) which were not initially identified at the time the patient was discharged from hospital.

Thus, by selecting only the Ile de France region (considered as being representative of the rest of France), the observational data could be used to implement a prospective study which would allow for a more specific approach to the long-term sequelae of childhood meningitis and meningococcal purpura fulminans. This would specifically include clinical, psychological and psychomotor assessments and a speech assessment. In addition, a survey addressed to the parents should help to assess their experience with the disease, to identify post-traumatic stress and to review the care pathway which had (or had not) been implemented since their child was discharged from hospital. This study will thus assess the consequences of these serious conditions with their medical and logistical care as well as the impact that they have on their relatives.

This study’s primary objective is to assess the long-term sequelae of childhood IMIs such as meningitis and purpura fulminans using a multidisciplinary psychological, intellectual, sensory and clinical approach. The secondary objective is to assess the social consequences and the perception of relatives regarding this serious condition, so that the true burden of the disease may be correctly measured by taking into account parameters which have not been considered to date.

Description of the condition

IMIs include all serious infections related to meningococci or *Neisseria meningitidis* (Nm). An invasive infection is defined by the isolation of a bacteria in a space which is normally sterile (blood, cerebrospinal fluid etc.) and the two main infections are meningitis and septicaemia (1). They may progress to septic shock including to purpura fulminans, the most lethal form of the disease. This is characterised clinically by extensive and rapidly necrotic, ecchymotic purpura combined with circulatory failure (2).

Nm is a bacterium which is specific to humans. In approximately 10% of the general population, it colonises the mucous membrane of the upper respiratory tract of humans without causing an IMI (3). In rare cases, some strains of Nm, known as hyperinvasive strains (4), can cross the respiratory epithelium and invade and multiply in the bloodstream, causing an IMI.

In industrialised countries (Europe, America and Oceania), the annual incidence varies from 0.7 to 2 cases per 100,000 inhabitants and mainly occurs in sporadic cases, with a predominance of strains of serogroups B and C. Thus, the incidence of IMI in France remains low (close to the average rate of 1 in 100,000 observed in Europe) but is higher in infants under the age of one (8.9 in 100,000 in 2015) and young adults aged 18–20 (1.5 in 100,000 in 2015) (5). The majority of cases occur sporadically and mainly relate to the B serogroups, which account for an average of 62% of cases (5).

It is a severe condition, as the mortality rate is from 8 to 10%, and it accounts for 50 to 60 deaths per year (5). It may reach much higher rates in the case of purpura fulminans (6). As regards the sequelae, immediate sequelae are well known but there are few studies which focus on the long-term sequelae and on the cognitive development of children. According to studies, sequelae secondary to an IMI at the end of hospitalisation were reported in 10 to 40% of cases (7–10). These are usually cutaneous (skin necrosis with more or less extensive loss of skin which may require a skin graft), orthopaedic (amputations), neurological (focal neurological deficits, epilepsy, spasticity, deafness), cognitive (learning disabilities), behavioural and psychological. The most common sequelae in children who have had an IMI appear to be skin necrosis (10%) and all types of neurological problems (10 to 12.2%) (11).

However, there are few prospective studies which focus on the later neuropsychological and developmental consequences for these children, and the rate of delayed sequelae is possibly being underestimated at the moment. The ongoing AMEND study is assessing these long-term sequelae in young adults (12), but a prospective study on children is also necessary. In fact, the latter seems essential to thoroughly assess the impact these IMIs may have on development, to obtain a more reliable estimate of the rate of sequelae and, above all, to be able to implement appropriate monitoring of these children.

Description of the relevant population

This study will involve children from 0 to 15 years of age who had meningitis or meningococcal purpura fulminans diagnosed in a hospital paediatric department in Ile de France between 2010 and 2019.

Benefit(s)

Few studies have reported on the long-term sequelae of childhood meningitis and meningococcal purpura fulminans at least one year after, and up to a maximum of 10 years after, their discharge from hospital. In terms of public health, this study should highlight the importance of a “flagged“ care pathway in these serious conditions which sometimes have delayed consequences.

This study will allow parents to have access to specialists, at no cost, allowing them to identify whether their child has experienced sequelae and allowing the implementation of a corresponding follow-up to improve the management of the child.

Risk(s) and obligation(s) attached to the research

The study does not involve any risks. The only obligation is the need to attend consultations with various specialists.

# Objectives of the research

Primary Objective

To assess the long-term (between one and ten years) physical, neurological or sensory sequelae from meningitis or meningococcal purpura fulminans.

Secondary Objectives

- Establish a course of care
- To assess medium/long-term post-traumatic stress on parents
- To assess the social impact of the disease: education of the children; activity of the parents

# Subject screening

Inclusion criteria

- Infants and children 1 to 15 years of age;
- Who had meningitis or meningococcal purpura fulminans included in the observatory between 2010 and 2019;
- One of the individuals with parental authority has read and understood the information letter and their express consent has been obtained;
- Patient affiliated with a social security scheme (Social Security or Universal Medical Coverage).

Exclusion criteria

- Refusal of either parent.

Enrolment Objective

Approximately 100 patients are expected to be enrolled in the study.

# Research methodology

This is an interventional study with minimal risks and obligations involving human subjects (RiPH2).

It is a multi-centre, prospective, non-randomised study.

Primary and secondary endpoints

### Primary endpoint

- Number of children with at least one neurological, skin, orthopaedic or sensory sequela.

### Secondary endpoint(s)

- Number of children who underwent a “flagged“ care pathway with the establishment of a score based on the consultations performed.
- Number of children with some severe neurological sequelae: hemiplegia etc.
- Number of children with orthopaedic complications (amputations etc.).
- Number of children with sensory disorders.
- Number of children with skin sequelae.
- Number of children with learning disabilities (with no identified neurological sequelae).
- Number of children with cognitive or psychological impairments identified on the WPPSI, WISC V or VINELAND. Care pathway followed by the children: number and type of follow-up consultations; Specialised paediatric consultations or not; ENT and speech therapy assessment/follow-up; neuro-developmental assessment.
- Parental post-traumatic stress assessment via the IES-R questionnaire.

# Performance of the study

Patient screening

The study will be offered to parents of children reported in the French National Observatory of Bacterial Meningitis in Children who are not deceased and have not been lost to follow-up. If the parents agree to participate in the protocol, and after the informed consent form has been obtained, the children will be enrolled.

Research procedure

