# Statistical aspects

Assessment of the number of subjects to be recruited

Between 2010 and 2019, 169 cases of meningitis and meningococcal purpura fulminans were declared in the French National Observatory of Bacterial Meningitis in Children. The initial clinical data for these patients are already known. After having excluded deceased patients (n = 9) and patients who have been lost to follow-up (approximately 20%, n = 30), and with an envisaged acceptance rate of 80%, 100 patients should be enrolled and follow the care pathway established as part of the study.

Analyses

The proportion and confidence interval of children with sequelae will be described for the entire recruited cohort within each age group and according to the type of sequelae: neurological, orthopaedic, skin, sensory or developmental. The qualitative data will be described by their number and percentage. The quantitative data will be described by their median and standard deviation. Kaplan Meier survival curves will be drawn to determine the presence of sequelae at various times after meningitis. Comparison tests will be performed to determine the presence of sequelae according to their severity or the initial onset.

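### The planned proportion with sequelae omits 35–38% of survivors, and the initial data already held are not used to check or adjust for this

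*Protocol*

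**What the plan says.** Section 8.1 (Patient screening) restricts the approach to observatory children "who are not deceased and have not been lost to follow-up". Section 6.2 then excludes a child if either parent refuses.

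Section 12.1 starts from the statement that "169 cases of meningitis and meningococcal purpura fulminans were declared in the French National Observatory of Bacterial Meningitis in Children". It removes 9 deaths and about 30 children lost to follow-up, and concludes that, "with an envisaged acceptance rate of 80%, 100 patients should be enrolled". The same section says: "The initial clinical data for these patients are already known". Section 4.1 gives part of those data for the 169 cases: "36 experienced short-term sequelae, 21 had neurological complications", with circulatory and other involvement making up the rest.

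Section 12.2 sets the proportion with sequelae and its confidence interval for all recruited children, by age group and type of sequela. It also plans comparison tests of sequelae by severity or initial onset. It mentions neither a comparison of participants with non-participants nor an estimate referred back to the survivors.

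The aims reach beyond the recruited children. Section 4.2 wants a firmer figure for how often sequelae occur, and section 4.1 wants the burden of the disease properly measured and treats the region as representative of France.

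**The concern.** A crude proportion among families who are still in contact and willing to attend describes those families. It describes survivors only if enrolment is unrelated to sequelae. Two routes could break that condition: whether a child can still be reached, and whether parents accept up to four specialist visits. Either could depend on how the child is doing. The planned confidence interval covers sampling error only and would show none of this.

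Most cohorts can do little about non-participants because they know nothing about them. Here the protocol says the initial data exist, including short-term sequelae, which could plausibly predict both enrolment and long-term outcome. The stated analysis does not use them for this purpose.

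**Working it through.** **Inputs from the protocol.** 169 cases, 9 deaths, about 30 (about 20%) lost, 80% acceptance and 100 enrolled (section 12.1); 36 children with short-term sequelae (section 4.1; 21 + 8 + 7 = 36).

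**The plan's own figure.**
- Survivors: 169 − 9 = 160.
- With 30 lost: (160 − 30) × 0.80 = 104.
- With 20% of 160 lost: (160 − 32) × 0.80 = 102.4.
- With 20% of 169 lost: (160 − 33.8) × 0.80 = 101.0.

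The stated 100 is a rounded-down version of these.

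**Share of survivors not enrolled.** At 104 enrolled: 56/160 = 35.0%. At 100 enrolled: 60/160 = 37.5%. The other two readings give 36.0% and 36.9%.

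**Possible bias.** Assumptions not in the protocol:
- all 36 children with short-term sequelae survived, so they are 36/160 = 22.5% of survivors;
- long-term sequelae occur in 80% of them and 10% of the others;
- children with short-term sequelae are r times as likely to be enrolled, with 100 enrolled in total.

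Rate among survivors: (36 × 0.8 + 124 × 0.1)/160 = 25.75%.
Share of the sample with short-term sequelae: s = 36r/(36r + 124).
Crude proportion: 0.8s + 0.1(1 − s) = 0.1 + 0.7s.

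| r | s | Crude | Bias (points) |
|---|---|---|---|
| 1.5 | 54/178 = 30.3% | 31.2% | +5.5 |
| 1.2 | 43.2/167.2 = 25.8% | 28.1% | +2.3 |
| 0.8 | 28.8/152.8 = 18.8% | 23.2% | −2.6 |
| 0.67 | 24.12/148.12 = 16.3% | 21.4% | −4.4 |

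The bias equals the gap in long-term risk times (s − 0.225). With assumed risks of 90% and 15% the gap is 0.75 instead of 0.70, and r = 1.2 to 1.5 gives +2.5 to +5.9 points.

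**Against sampling error.** 95% half-width at n = 100: 1.96 × √(0.281 × 0.719/100) = 8.8 points at 28.1%, and 1.96 × √(0.312 × 0.688/100) = 9.1 points at 31.2%. The bias for r = 1.2 to 1.5 is therefore roughly a quarter to three fifths of the half-width.

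**What post-stratification does.** Weighting the two stratum proportions by 36/160 and 124/160 gives 0.225 × 0.8 + 0.775 × 0.1 = 25.75% whatever r is, provided enrolment within each stratum is unrelated to long-term outcome.

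**The case against.** - *This belongs in a statistical analysis plan.* Weighting details usually do, and none is at hand. Section 12.2 also does not forbid an additional estimate. But the protocol itself chooses the crude proportion in recruited children as its result and records that the data for a better one are held. The point concerns that choice, not missing detail.
- *The bias must be upward.* A reader might infer that children who recovered well drop out or decline, so that the crude figure is too high. The protocol gives no reasons for loss or refusal. Section 4.4 offers free specialist access, which could draw families with worries or families whose child was never assessed. Families of badly affected children might also decline. Both signs are possible.
- *The bias can equal the whole half-width.* Under the 80%/10% risks this needs all 36 children with short-term sequelae among the 100 enrolled: 0.1 + 0.7 × 0.36 = 35.2%, a bias of about 9.4 points against a half-width of 9.4. That means no loss and no refusal in that group. A different model, in which long-term sequelae themselves raise enrolment 1.5-fold at an assumed true rate of 30%, gives +9.1 points (and −7.7 at a ratio of 0.67). Weighting on short-term sequelae would remove only part of that.
- *The sampling frame drops children no longer seen in clinic.* The protocol does not say so. Section 8.2.1 has an arm for children not being monitored, and section 8.2.2 gives their parents a list of professionals. No change to section 8.1 follows.
- *The initial data are used.* They appear to be, in the comparison tests by severity or initial onset. Those tests concern enrolled children and say nothing about the rest.

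**Conclusion.** The concern holds in a limited form. Some 35–38% of survivors will be absent from the estimate, and section 12.2 neither describes how they differ nor adjusts for it, although initial data are held. The non-enrolled share is the protocol's own arithmetic. The bias of about 2 to 5.5 points, against a half-width of about 9, is illustrative: it rests on assumed risks of 80% and 10%, assumed enrolment ratios of 1.2 to 1.5, and all 36 children having survived. Ratios below 1 give a bias of similar size in the other direction. It would be wrong to say that the proportion is known to be overstated, or that the bias is shown to match the sampling error.

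One further limit: section 6.1 restricts eligibility to ages 1 to 15, and the protocol does not say how many of the 160 meet this. The population to weight to is the age-eligible survivors, which may be fewer than 160.

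**What to change.** In section 12.2:

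1. Add a table comparing enrolled with non-enrolled age-eligible survivors on registry data: age at infection, meningitis or purpura fulminans, short-term sequelae, and year.
2. Report the primary proportion twice: crude, and post-stratified to the age-eligible survivors with a confidence interval that accounts for the weights. Keep the strata coarse (short-term sequelae yes or no, and age group only if numbers allow), since only 36 children had short-term sequelae.

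Post-stratification needs only counts per stratum for the non-enrolled. Inverse-probability weights would need individual or cross-classified records.

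The cost is one table and one extra estimate, with no added patients or visits. Unequal weights by themselves widen the interval slightly. At r = 1.5 the variance factor is 100 × (36²/30.3 + 124²/69.7)/160² = 1.03, or about 1.5% in width; a stratifier that predicts the outcome well may offset this. Only bias explained by the registry variables is removed, and the report should say so.
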